#### Screening Baseline Visit

Potential subjects were screened by phone interview after providing verbal consent. Those who met all inclusion criteria were scheduled for an SBV. After administering informed consent, subjects attending the SBV were asked to answer questionnaires and provide sociodemographic data **,** consent to a brief physical exam and a fasting blood draw for study measures, receive a Fitbit Zip accelerometer, and attend a mobile phone and Fitbit Zip training session.

#### Run-In Period

After the SBV, eligible subjects immediately started a two-week run-in period, during which they were asked to wear a Fitbit Zip every day for at least 10 hours/day, and send photos of all food and drinks consumed for three consecutive days. Study eligibility required a 70% adherence rate, at minimum.

#### Fitbit Zip and App/Diary Training

Prior to starting the run-in period, eligible subjects received training on how to use the Fitbit Zip and download the app. Subjects who did not own a smartphone used their own tablets or personal laptops. At the randomization visit, only intervention group subjects were trained on how to download and use the Fitbit app/diary, and asked to input their daily food/drinks and calorie intake, and weekly weight. Active control group subjects were only trained to use the Fitbit Zip and download the app until the 3-month time point. After the 3-month control period, control subjects were trained to use the Fitbit app/diary when they received the intervention program.

All participants were asked to provide an overnight plan to store their Fitbit Zip. This information was used to initiate a recovery protocol if equipment was lost, and included a comprehensive interview to help subjects reconstruct step-by-step events of the previous 24 hours. Based on previous studies, this recovery protocol was 98% successful [29,30].

#### Facebook Training

Subjects receiving the intervention program received training to access and use the private Facebook group, with education on appropriate Facebook etiquette. Prior to joining the private Facebook group, each subject was assigned a secure email account (excluding personal information) for the PilAm Go4Health private Facebook group.

#### Randomization and Blinding

At the end of the two-week run-in period, subjects able to adhere to the run-in requirements 70% of the time were randomized to either the intervention group or active control group in a 1:1 ratio. A permuted block randomization method stratified by gender was used with randomly selected block sizes of 2 and 4. Prior to the trial, the study statistician created a computer-generated random allocation sequence. Investigators, research staff (who conducted anthropometric measures, entered data, and undertook data management), and study participants were unblinded during the study, but personnel performing the lab sample evaluations were blinded to treatment groups.

##### Intervention Group

Only subjects randomized to the intervention group immediately received the PilAm Go4Health intervention. Participants were asked to wear their Fitbit Zip at least 10 hours/day and use the Fitbit app/diary to input and track their daily food/drink and calorie intake, and to record their weight twice per week (Monday and Friday). Subjects received individually tailored goals, in-person intervention meetings, Fitbit Zip and Fitbit app/dairy training, and private Facebook group training (and an invitation to join the study Facebook group). Each subject’s baseline weight, PA, and diet information were used to tailor their intervention for short-term and long-term goals. Based on each subject’s progress during the study, they received tailored feedback and coaching, including barrier and support assessments, and information regarding the benefits of tracking health behaviors on the Fitbit Zip and Fitbit app/diary. Research staff monitored each subject’s Fitbit Zip and Fitbit app/diary data (step-counts, food/drink and calorie intake, and weight), and Facebook logins, likes, and posts. All automatically recorded Fitbit Zip data were wirelessly uploaded to each subject’s individual study Fitbit and Facebook account for storage on study data servers. Table 1 displays an overview of topics covered at each in-person office visit, and during private Facebook group participation.

##### Active Control Group

Subjects randomized to the active control group were asked to continue to only use the Fitbit Zip every day. During the randomization visit, each active control participant received Hepatitis B education, including the National Digestive Diseases Information - Hepatitis B handout for Asians and Pacific Islanders [34].

#### Office Visits - 1 Month Through 6 Months

After the randomization visit, intervention group subjects were asked to return once per month for three months, for intervention education, coaching, and support. At the 3-month visit, subjects transitioned to the 3-month maintenance, and were asked to return for a 4-month progress evaluation and 6-month office visit. Active control group subjects were asked to return at the 1-month visit for a progress evaluation, and received Hepatitis C education. After completing the 3-month control period, active control subjects transitioned to receive the PilAm Go4Health intervention, and were asked to return for intervention follow-up visits at four, five, and six months. At the final 6-month office visit, all subjects completed the PilAm Go4Health study (see Figure 1).

At the 3-month office visit, all intervention and control subjects were asked to answer questionnaires and consent to a physical exam and fasting blood draw. Intervention subjects were asked to participate in a post-program process evaluation (semi-structured interview) before transitioning to the 3-month maintenance program.

At the 6-month office visit, all intervention and control group subjects were asked to complete questionnaires, consent to a physical exam and a final fasting blood draw, and participate in a post-program process evaluation (semi-structured interview). All subjects completed the study at this visit, and were removed from the Fitbit study account and private Facebook group account. Subjects who completed the 6-month study were allowed to keep their Fitbit Zip, and research staff assisted subjects in setting up their own personal Fitbit accounts.

### Outcome Measures

Primary and secondary outcomes were measured at baseline, 3 months, and 6 months. Process evaluations were collected only at 3 and 6 months. During the analysis phase of this project, the primary outcome will be percent change in body weight, while secondary outcomes include changes in waist circumference, fasting plasma glucose, HbA1c levels, step counts, and dietary fat and sugar-sweetened beverage intake. Participants also provided feedback on the intervention program regarding cultural relevancy, compliance to the mobile phone-based intervention, compliance to the virtual social networking, barriers to use, perceived efficacy, and suggestions for intervention improvements.

In addition to the primary and secondary outcomes, self-reported information regarding self-efficacy for PA and social support were collected at baseline, 3 months, and 6 months. Sociodemographics, health literacy, and acculturation data were collected only at baseline. Table 2 presents all study questionnaires, planned administration, evidence of validity and reliability, and references.

**Table 2 table2:** PilAm Go4Health outcome measures and surveys/questionnaires.

Outcomes		Time of collection	Scale / Collection Method
**Primary Outcomes**			
	BMI, weight, height, and waist circumference	Baseline, 3 months, and 6 months	(1) Weight measured with Professional Digital Floor Scale
			(2) Height measured with Healthometer PORTROD Height Rod
			(3) Waist circumference (standing) measured with a tape measure midway between lower rib margin and iliac crest [35]
			(4) BMI = kg/m2
	Fasting plasma glucose & HbA1c	Baseline, 3 months, and 6 months	Venipuncture blood specimen collected at the Clinical and Translational Science Institute Clinical Research Service Center
**Secondary Outcomes**			
	Physical activity	Baseline, 3 months, and 6 months	(1) Objectively measured total daily step-counts collected by the Fitbit Zip and mHealth app
			(2) Self-reported International Physical Activity Questionnaire [36] - 27 items (Cronbach alpha median 0.80)
	Diet	Baseline, 3 months, and 6 months	(1) Fat-Related Diet Habits Questionnaire [35,37] - 22 items (Cronbach’s alpha = 0.77)
			(2) Beverage Intake Questionnaire [38] - 15 items (Cronbach’s alpha range 0.97 to 0.99)
**Other Outcomes**			
	Self-efficacy for physical activity	Baseline, 3 months, and 6 months	Self-efficacy for Physical Activity Questionnaire [39] - 12 items (Cronbach alpha range 0.78 to 0.82)
	Self-efficacy for diet	Baseline, 3 months, and 6 months	Eating Confidence survey [39,40] -16 items (Cronbach alpha range 0.83 to 0.84)
	Social support for diet and exercise	Baseline, 3 months, and 6 months	Social Support for Diet and Exercise Survey [41] – 23 items (Cronbach alpha range 0.80 to 0.93)
	Self-reported health	Baseline, 3 months, and 6 months	Patient-Reported Outcomes Measurement Information System Survey Global Health [42] - 10 items (internal consistency=0.81, validity=0.86)
	Process evaluations	3 months and 6 months	Comprehensive, semi-structured interviews to solicit participant feedback on cultural relevancy, compliance to the mobile intervention, barriers to use, and suggestions for intervention improvements (at 3 and 6 months)
**Baseline Outcomes**			
	Sociodemographics and medical history	Baseline only	Gender, ethnicity, birth date, primary language, years lived in United States, marital status, number of children, education level, employment and health insurance status, income, hyperlipidemia, smoking, hypertension or other chronic illnesses, and/or family history of diabetes
	Acculturation	Baseline only	Marin Short-Acculturation Scale for Filipino Americans [43] - 12 items (Cronbach alpha range 0.79 to 0.85)
	Health literacy	Baseline only	Short-Health Literacy Survey [44,45] - 3 items (Reliability range 0.74 to 0.84)

### Data Collection

Data were collected during in-person office visits, via self-reported PA and diet, and through the Fitbit Zip and Fitbit mHealth app/diary. In-person data included questionnaires and anthropometric data that were collected during research office visits. Self-reported PA and diet included questionnaires on PA (days per week, type, and duration of exercise), and diet (sugar-sweetened beverage intake, fat related diet intake) that will be collected along with self-efficacy and social support for phsycial activity. See Table 2 for questionnaire details. All study data were entered via encrypted computers and transferred to the research study's secure database servers. Likewise, participants’ oral responses obtained from semi-structured interviews will be coded and stored on the same secure encrypted research study database servers. Fitbit Zip and app/diary data were wirelessly uploaded and transmitted in real-time directly to secure Fitbit database servers that identify participants only by their assigned Gmail account (no personal information was transferred). In turn, the study Fitbit account was tied to a secondary Fitabase database server that included all participants in our secure study Fitbit account. Fitabase is a secure confidential research platform that collects data from Internet-connected consumer devices, such as Fitbit accelerometers and mHealth apps. Fitabase aggregates data, allowing researchers to easily organize, analyze, and export data gathered from study participants. Research staff have access to all participants’ Fitbit data (step-counts, weights, and food/calorie intake) through the study Fitabase account.

### Data Analyses

Regarding aim 1 of the study, feasibility will be assessed based on recruitment (eligible participants who were screened, completed the run-in, enrolled, and randomized), adherence (during the 3-month intervention, at least 70% compliance with the Fitbit Zip, mHealth app, and weight and calorie diary), and retention (6-month program retention and attrition rate). All results will be tabulated by study arm, and reported with descriptive statistics and effect sizes or 95% confidence intervals.

Descriptive statistics will be used to analyze the sample characteristics pertaining to aim 2 of the study. Prior to the analyses, validity of the randomization will be checked by assessing the randomized groups for characteristics measured before randomization using chi-square, Fisher's exact tests, t-tests, and nonparametric rank tests, as appropriate. If potentially confounding imbalances are found, we will adjust the between-group analyses for potential confounders of treatment assignment. The primary analysis will use analysis of covariance to compare primary and secondary outcomes at 3 months by arm, controlling for baseline levels. Outcomes will be transformed as necessary to meet assumptions of normality and equal variance. In a supplementary analysis (for more efficient data use), we will include on-treatment outcomes analysis for the control group at 6 months, using a linear mixed model to account for the repeated measures on waitlist controls, and include a smooth function of time to reduce potential bias from secular effects. In addition, we will assess within-group changes in the immediate intervention group between 3 and 6 months, as a preliminary measure of the durability of the intervention effect in the maintenance phase. We will also use these models to estimate residual variances and within-person correlation, which will be crucial to future trial planning. Exploratory mediation analysis will be conducted to test the association between step-counts and diet on change in outcomes.

Aim 3 will be assessed using semi-structured interview methods. At the 3-month post-intervention time point, participants’ qualitative perspectives on their experience during the intervention (advantages, barriers, and support) and use of mobile technology (perceived usefulness, ease of use) were obtained. Qualitative data will be coded and analyzed. Transcripts will be independently coded for initial themes and then checked for inter-rater agreement by at least two research investigators. Content analysis will be conducted by marking and categorizing key words and phrases to identify emerging themes [46,47]. Data analysis will identify links across themes. Themes will be reviewed, discussed, and resolved through consensus. The research team will meet to review and discuss transcript-coding, achievement of data saturation, consensus regarding identification and definition of themes, and selection of illustrative excerpts from transcripts. Dependability of the data interpretation will be supported by investigator triangulation, a process whereby more than one investigator analyzes the data [48]. Themes derived from the data will be used to refine and further culturally tailor the intervention, in preparation of a larger full-scale RCT proposal.

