## Results

### Baseline Data

Study participants were recruited, enrolled, and randomized between December, 2014 and January, 2016. Of the 57 potentially eligible participants who completed the SBV and two-week run-in period, 45 were eligible for study enrollment, and were randomized into one of two groups: the PilAm Go4Health intervention group (n=22) or the active control group (n=23). See Figure 3 for details.

Table 3 presents the baseline characteristics of study participants. Overall, the mean age of participants was 57.6 (standard deviation [SD] 9.8) years with approximately one-third of the cohort being male (38%, 17/45) and two-thirds female (62%, 28/45). More than half of all participants had completed college (56%, 25/45), were married/cohabitating (67%, 30/45), and employed full or part time (69%, 31/45). The majority of participants were Filipino immigrants (84%, 38/45) who had lived in the United States for more than 10 years, and close to half (47%, 21/45) had 3-to-5 people living in their household. Overall, participants were in the obese BMI category, with a mean BMI of 30.2 kg/m^2^(SD 4.9) and were in the high disease-risk category with a mean waist circumference of 100.0 cm (SD 11.5) [49]. The mean fasting blood sugar level was 140.4 mg/dL (SD 27.5) and mean HbA1c was 7.4 (SD 0.99) within blood test levels for diabetes [50]. Participants in the intervention group were all Filipino immigrants (100%, 22/22), whereas 30% (7/23) of the active control group participants were born in the United States. Comparisons of baseline characteristics demonstrated two statistically significant differences (*P*<.05) between the intervention and control groups: years lived in the United States, and BMI.

**Table 3 table3:** Baseline sociodemographics, anthropometrics, and serum lab results.

Variable		N=45 Mean (SD) or % (n)	Intervention N=22 Mean (SD) or % (n)	Control N=23 Mean (SD) or % (n)	*P*-value
Age in years		57.6 (9.8)	57.4 (9.8)	57.7 (10.0)	0.90
Race (Filipino)		100 (45)	100 (22)	100 (23)	1
Gender					0.85
	Male	37.8 (17)	36.4 (8)	39.1 (9)	
	Female	62.2 (28)	63.6 (14)	60.9 (14)	
Marital status					0.063
	Never married	11.1 (5)	4.5 (1)	17.4 (4)	
	Divorced/widowed	22.2 (10)	31.8 (7)	13.0 (3)	
	Married/cohabitating	66.7 (30)	63.6 (14)	69.6 (16)	
Education					0.67
	Some college	24.4 (11)	18.2 (4)	30.4 (7)	
	Completed college	55.6 (25)	63.6 (14)	47.8 (11)	
	Graduate school	20.0 (9)	18.2 (4)	21.7 (5)	
Employed					0.21

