	Full or part time	68.9 (31)	77.3 (17)	60.9 (14)	
	Unemployed	4.4 (2)	4.5 (1)	4.3 (1)	
	Retired	26.7 (12)	18.2 (4)	34.8 (8)	
Years lived in the United States					0.003*
	Native born	15.6 (7)	0 (0)	30.4 (7)	
	5 to 9 years	2.2 (1)	0 (0)	4.3 (1)	
	10 years or more	82.2 (37)	100 (22)	65.2 (15)	
Number living at home					0.82
	<3	42.3 (19)	40.9 (9)	43.5 (10)	
	3 to 5	46.7 (21)	50.0 (11)	43.5 (10)	
	>5	11.1 (5)	9.1 (2)	13.0 (3)	
Previous pedometer use					0.41
	Yes	33.3 (15)	27.3 (6)	39.1 (9)	
	No	66.7 (30)	72.7 (16)	60.9 (14)	
Outcome measures					
	Weight (kg)	75.8 (17.0)	71.6 (9.1)	80.3 (22.3)	0.21
	Waist circumference (cm)	100.0 (11.5)	97.4 (8.2)	102.8 (14.1)	0.24
	BMI (kg/m^2^)	30.2 (4.9)	28.4 (3.3)	32.2 (5.7)	0.048*
	Fasting glucose (mg/dl)	140.4 (27.5)	135.8 (23.1)	145.3 (31.7)	0.39
	HbA1c (%)	7.40 (0.99)	7.26 (0.89)	7.55 (1.09)	0.45
	Steps (steps/day)	7431 (1789)	7142 (1475)	7743 (2091)	0.40

* *P*<0.05 between group difference in baseline characteristics.

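### Covariates for the between-group analyses are to be chosen by baseline significance tests, and the stated primary ANCOVA leaves out gender, the only stratification factor

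*Protocol article*

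**What the plan says.** Protocol article, Data Analyses (aim 2), has three steps.

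- Before the analyses, "validity of the randomization will be checked by assessing the randomized groups for characteristics measured before randomization". The tools are chi-square, Fisher's exact, t and rank tests.
- Adjustment then depends on the result: "If potentially confounding imbalances are found, we will adjust the between-group analyses for potential confounders of treatment assignment". No threshold and no list of candidate covariates is given.
- The main model is an ANCOVA: "The primary analysis will use analysis of covariance to compare primary and secondary outcomes at 3 months by arm, controlling for baseline levels".

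Randomization and Blinding states that allocation was 1:1 in permuted blocks of 2 and 4, stratified by gender and nothing else. Gender is not named in the analysis model.

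Baseline Data shows the comparison already carried out. It "demonstrated two statistically significant differences (*P*<.05) between the intervention and control groups: years lived in the United States, and BMI". Table 3 places all 22 intervention participants in the category of 10 years or more in the United States. The 23 controls are 7 native born, 1 with 5 to 9 years and 15 with 10 years or more.

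**The concern.** A covariate is worth including when it predicts the outcome, or when the design used it. A between-arm P value at baseline measures neither. If allocation was sound, any baseline difference arose by chance, and a small P value does not show that the variable predicts weight change. The rule also tends to miss the variable that most clearly belongs in the model: gender was balanced by stratification, so a search for imbalance will almost never pick it (Table 3: P=0.85).

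What is at stake is the between-group estimate for the primary and secondary outcomes, which is the purpose of aim 2. Data Analyses also intends to carry residual variances from its models into planning of a larger trial. With the rule as written, the covariate set depends on how the baseline table happened to fall and on an undefined judgement of what is potentially confounding. One of the two flagged variables overlaps so little between arms that adjusting for it could cost noticeable precision.

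**Working it through.** **Inputs.** Arm sizes of 22 and 23 (Baseline Data). Years in the United States, as native born / 5 to 9 years / 10 years or more: 0/0/22 intervention and 7/1/15 control (Table 3). Gender as the only stratification factor (Randomization and Blinding).

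**1. The printed P value for years in the United States.** Table 3 gives 0.003. A Wilcoxon rank-sum test on the three ordered categories has a U statistic of 341 against an expected 22×23/2 = 253. The tie-corrected variance is (506/12) × [46 − 50,952/1,980] = 854.6, so the SD is 29.23. With continuity correction z = 87.5/29.23 = 2.99 and P = 0.0028, which rounds to the printed figure. Pearson chi-square (0.0095) and the exact test (0.0060) on the same counts are also below 0.05. The article allows rank tests, so the printed value is not in dispute.

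For BMI, a t-test from the printed means and SDs with 22 and 23 gives P = 0.009, against 0.048 printed. A different test or fewer observations could explain this. Either way it is below 0.05.

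**2. How easily the tests flag something.** Leaving out race, Table 3 has 14 tested rows. If these were independent tests at 0.05 under sound randomisation:

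- expected number flagged: 14 × 0.05 = 0.7
- chance of at least one: 1 − 0.95^14 = 0.51

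This is illustrative only. Weight, waist and BMI are related, and gender was balanced by design.

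**3. The treatment contrast if years in the United States were adjusted for.** The variance of the simple treatment contrast is the residual variance times a factor that depends on the design.

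| Model | Factor | Variance ratio | SE ratio | Controls with zero weight |
|---|---|---|---|---|
| No years covariate | 1/22 + 1/23 = 0.0889 | 1.00 | 1.00 | 0 |
| Table 3 categories, or 10 years or more vs other | 1/22 + 1/15 = 0.1121 | 1.26 | 1.12 | 8 |
| Native born vs immigrant | 1/22 + 1/16 = 0.1080 | 1.21 | 1.10 | 7 |
| Linear score 0/1/2 | 0.1111 | 1.25 | 1.12 | none exactly |

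In the second row the category terms absorb the 8 controls, since no intervention participant shares their categories. Each of the other 15 controls carries weight 1/15. With the linear score, each native-born control has weight 0.002, against −0.066 for each control with 10 years or more.

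These ratios hold residual variance fixed and assume that all 45 have a 3-month outcome. Ignoring degrees of freedom, the adjusted SE would break even if the covariate cut residual variance by 1 − 0.0889/0.1121 = 21%.

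**4. BMI.** For the weight outcome, baseline weight is already the baseline covariate, and BMI is computed from weight, so the two overlap. The article gives no correlation. For glucose, HbA1c, steps and diet, baseline weight is not in the model and this overlap does not arise.

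**The case against.** The best defence is that the rule is milder than it looks. It sets no P threshold, and the words about potential confounding call for judgement. The check precedes the analyses and uses only pre-randomisation data, so outcomes cannot steer it. Covariate lists are often left to an analysis plan, and this is a 45-person pilot.

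Much of this stands, and it rules out several stronger readings that a reader might infer:

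- **That adjustment for years in the United States or BMI is already committed.** The article reports the two differences and stops.
- **That 8 controls would be discarded.** They would stay in the ANCOVA and inform the baseline slope and residual variance. The count also depends on coding. If years of residence were entered as a continuous variable, native-born controls might overlap with long-resident intervention participants, and zero weight would not follow.
- **That the baseline tests say nothing about the randomisation.** They can give weak evidence of subverted allocation, which is not an idle question with unblinded staff and small blocks. They remain a poor way to choose covariates.
- **That the rule creates rival primary results.** It leads to an adjusted or an unadjusted analysis and does not call for both.

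The core is not answered. Baseline tests are the only stated way of finding imbalances, Baseline Data applies P<.05, and the stated model omits the one factor that the design used. That is a rule the article states, not a detail it leaves open.

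**Conclusion.** The concern holds in a limited form. Adjustment of the between-group analyses is made to depend on baseline tests, which select by chance imbalance and not by prognostic value. The primary ANCOVA as stated omits gender.

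The possible cost can be sized but is conditional. If years in the United States were entered in the Table 3 categories, the simple treatment contrast would compare 22 with 15, and its SE would be about 12% larger (10% with native born versus immigrant). This assumes unchanged residual variance and complete 3-month data. A prognostic covariate would offset some or all of the loss. The 51% chance of at least one flag assumes 14 independent tests and shows only that such a rule fires readily.

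Severity is moderate. The rule governs the main efficacy comparison, but the trial is a pilot seeking preliminary estimates and nothing yet commits it to the costly adjustment.

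**What to change.** Remove the sentence that makes adjustment depend on imbalances found, and put a fixed model in its place. For example: for each outcome, the primary analysis is an ANCOVA of the 3-month outcome on arm, the baseline value of that outcome and gender; no covariate will be added because of baseline comparisons. For percent weight change, the baseline value is baseline weight.

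Present Table 3 descriptively, without P values. If allocation integrity is a worry, review the allocation records directly.

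Confine adjustment for BMI, and any analysis of years in the United States, to labelled sensitivity analyses. One option for the latter restricts the comparison to the Table 3 category of 10 years or more. That also compares 22 with 15, so it shows robustness and does not restore precision. It should state how native-born participants are handled, since their own years of residence may exceed 10.

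State openly that this choice was made after the baseline data were seen. The Abstract says that analyses are underway, so record the date of the decision and whether 3-month outcomes by arm were known by then.

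The cost is a sentence or two in the analysis section and one fewer degree of freedom for gender. The downside is that the visible baseline imbalances are addressed only in sensitivity analyses.

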**Methods:**

This study was a 3-month mobile phone-based pilot randomized controlled trial (RCT) weight loss intervention with a wait list active control, followed by a 3-month maintenance phase design for 45 overweight Filipinos with T2D. Participants were randomized to an intervention group (n=22) or active control group (n=23), and analyses of the results are underway. The primary outcome will be percent weight change of the participants, and secondary outcomes will include changes in waist circumference, fasting plasma glucose, glycated hemoglobin A1c, physical activity, fat intake, and sugar-sweetened beverage intake. Data analyses will include descriptive statistics to describe sample characteristics and a feasibility assessment based on recruitment, adherence, and retention. Chi-square, Fisher's exact tests, t-tests, and nonparametric rank tests will be used to assess characteristics of randomized groups. Primary analyses will use analysis of covariance and linear mixed models to compare primary and secondary outcomes at 3 months, compared by arm and controlled for baseline levels.

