### Sample

The proposed sample size of 45 is conventional for pilot studies, with attrition estimated at 10%, for a final sample of 40 participants. Inclusion and exclusion criteria were based on American Heart Association metabolic syndrome risks, diagnosis, and management, as well as the DPP trial [1,10]. Key inclusion criteria included: (1) self-identified as Filipino; (2) age >18 years; (3) World Health Organization body mass index (BMI) cut-point for Asians >23 kg/m^2^for public health action [21]; (4) physician diagnosed T2D confirmed by clinical data (eg, documentation of fasting blood glucose >100 mg/dL, a positive oral glucose tolerance test >200 mg/dL, or HbA1c >6.5%); (5) noninsulin dependent T2D; and (6) own a smartphone, tablet, or laptop computer. Key exclusion criteria included: (1) uncontrolled T2D (fasting blood glucose >200 mg/dL); (2) disabilities precluding ability to walk for 20 minutes; (3) glucose metabolism-associated disease (Cushing's syndrome, Acromegaly, or Pheochromocytoma currently under treatment, or chronic pancreatitis). A detailed list of inclusion/exclusion criteria are presented in Multimedia Appendix 1.

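### Randomization was stratified by gender, but the stated primary ANCOVA has no gender term and its rule for adding covariates cannot bring gender in; if gender is prognostic, the intervals are wider than necessary

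*Protocol article*

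**What the plan says.** - **Allocation** (protocol article, Randomization and Blinding). Participants "were randomized to either the intervention group or active control group in a 1:1 ratio". The method is given as: "A permuted block randomization method stratified by gender was used with randomly selected block sizes of 2 and 4".
- **Primary model** (Data Analyses). "The primary analysis will use analysis of covariance to compare primary and secondary outcomes at 3 months by arm, controlling for baseline levels". Gender is not named. The Methods paragraph of the abstract gives the same specification.
- **Route to further covariates** (Data Analyses). Baseline characteristics are first compared between arms with significance tests, and then: "If potentially confounding imbalances are found, we will adjust the between-group analyses for potential confounders of treatment assignment".
- **What those tests found** (Baseline Data and Table 3). Two characteristics differed at the 5% level: "years lived in the United States, and BMI". Gender did not: 8 of 22 men in the intervention arm, 9 of 23 in the control arm, P=0.85.
- **Size** (Sample). "The proposed sample size of 45 is conventional for pilot studies, with attrition estimated at 10%, for a final sample of 40 participants".
- **Later use** (Data Analyses). The residual variances from the models are meant to inform planning of a larger trial.

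**The concern.** Stratified blocking removes most gender-related variation from the comparison of arms. A model without gender still counts that variation as residual noise. The reported standard error then describes a less precise design than the one that was run.

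The covariate rule adds to the mismatch. It admits variables because they happen to be imbalanced, and stratification exists to stop gender from being imbalanced. The one factor built into the design is therefore the one that the rule cannot select.

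At stake are the width of the intervals in a trial expecting about 40 completers, and the residual variance handed to a successor trial if that trial adjusts for gender.

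**Working it through.** **1. Reproduce the article's own figures.**
- Sample size: 40 / (1 - 0.10) = 44.4, rounded up to 45, as stated.
- Gender P-value: chi-square without continuity correction = 45 × (8×14 - 14×9)² / (22×23×17×28) = 45 × 196 / 240,856 = 0.037, so P=0.848. Table 3 gives 0.85.

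**2. Can the imbalance rule admit gender?** With blocks of at most 4, the arms can differ by at most 2 within each gender. With 17 men the difference is 1. With 28 women it is 0 or 2. The worst split is 8 men and 15 women against 9 men and 13 women. Its chi-square is 45 × (8×13 - 15×9)² / (23×22×17×28) = 45 × 961 / 240,856 = 0.18, P about 0.67. A 5% test cannot flag gender under this scheme.

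**3. Formula for the loss.** Let R2 be the share of residual variance that gender explains after baseline and any other covariates in the model. The document does not give it, so it is an assumption, ranged from 0 upward. Ignoring the single degree of freedom, interval width without gender divided by width with gender = 1/√(1 - R2):
- R2 = 0: 1.000
- R2 = 0.05: 1/√0.95 = 1.026
- R2 = 0.10: 1/√0.90 = 1.054
- R2 = 0.20: 1/√0.80 = 1.118

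**4. Check by simulation.** 20,000 trials per setting, no treatment effect, N = 45 with 17 men, gender-stratified permuted blocks of 2 and 4. ANCOVA on arm + baseline was compared with arm + baseline + gender. Intervals are 95% and tests are two-sided at 5% (assumed).

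| R2 | Model SE, no gender | True SE, no gender | Rejection, no gender | Rejection, with gender | Mean width, no gender / with gender | Ratio |
|---|---|---|---|---|---|---|
| 0 | 0.300 | 0.302 | 5.05% | 5.03% | 1.2105 / 1.2121 | 0.999 |
| 0.05 | 0.308 | 0.300 | 4.32% | 4.81% | 1.2415 / 1.2103 | 1.026 |
| 0.10 | 0.317 | 0.304 | 3.94% | 5.00% | 1.2812 / 1.2147 | 1.055 |
| 0.20 | 0.337 | 0.305 | 2.95% | 5.10% | 1.3600 / 1.2125 | 1.122 |

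The simulation agrees with the formula to within about half a percentage point. With gender in the model, the model SE is about 0.300 at every R2, against a true SE of 0.300 to 0.303. At N = 40 (15 men, assumed) the ratios are nearly the same: 1.2893/1.2918 = 0.998, 1.3254/1.2926 = 1.025, 1.3632/1.2920 = 1.055 and 1.4507/1.2927 = 1.122.

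**5. What the assumed R2 values mean.** With a male share of 17/45, the variance of the gender indicator is 0.378 × 0.622 = 0.235. The difference between men and women in residual SDs is √[R2 / (1 - R2) / 0.235]:
- R2 = 0.05: about 0.47 SD
- R2 = 0.10: about 0.69 SD
- R2 = 0.20: about 1.03 SD

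**The case against.** **The covariate set is not closed.** A reader might infer that the ANCOVA adjusts for baseline and nothing else. The article does not say that. Under its imbalance rule, BMI and years lived in the United States may enter. This stands, and it limits the claim. R2 must be read as what gender adds beyond those terms too. Baseline weight and BMI together largely encode height, which may stand in for part of gender.

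**This is a condensed article and the analysis plan is not shown.** An unseen plan could add gender. That is fair, but the article is not silent here. It names its covariate and fixes a rule for adding more, and step 2 shows that gender cannot pass that rule.

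**The size is assumed.** A reader might infer that the intervals are certainly too wide. The document gives no outcome data by gender, so zero belongs in the range. The primary outcome is percent change, already scaled to each person's own weight, and nothing in the article supports a difference as large as 1 SD. This stands in full.

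**The harm is limited.** A reader might infer that the treatment estimate or its test is invalid. It is not, because the error is only in the conservative direction. The article also presents its efficacy results as preliminary estimates and makes no power claim. This stands and keeps the severity low.

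**The residual variance is not wrong for every purpose.** A successor trial that does not adjust for gender needs the variance without gender. It is overstated only for one that does adjust.

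**Conclusion.** The point holds in a limited form. The stated primary analysis leaves out the stratification factor, and its own covariate rule cannot bring it in. If gender is prognostic beyond the other terms in the model, standard errors are too large and the intervals are about 2.6%, 5.4% and 11.8% wider than with gender included, at assumed R2 of 0.05, 0.10 and 0.20. If gender is not prognostic, nothing is lost. These figures rest on the stated blocking scheme, 40 to 45 participants analysed, and an R2 that the document does not supply. The direction is well supported; the size is unknown. No conclusion of the trial is made invalid. It is a free improvement of low severity.

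**What to change.** Specify gender as a covariate, whatever the observed balance, in:
- the primary ANCOVA for the primary and all secondary outcomes: 3-month outcome on arm + baseline value + gender, plus any covariates that the imbalance rule adds;
- the supplementary linear mixed model.

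Justify the term by the randomization scheme. The abstract says that analyses are already underway, so record that the choice follows from the design and not from the results. Report the residual variance with gender in the model, for planning a successor trial that adjusts for gender. Keep the variance without gender for a trial that would not.

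The cost is one degree of freedom: 42 to 41 residual degrees of freedom with 45 analysed, or 37 to 36 with 40, counting intercept, arm and baseline in the smaller model. If gender has no prognostic value, the interval widens by about 0.1% at N = 45 (1.2121/1.2105) and 0.2% at N = 40 (1.2918/1.2893). Gender is already collected.
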